# Effects of vitamin D supplementation on liver fibrogenic factors in non-alcoholic fatty liver patients with steatohepatitis: study protocol for a randomized clinical trial

**DOI:** 10.1186/s13063-019-3241-7

**Published:** 2019-03-04

**Keywords:** Trial protocol, Non-alcoholic fatty liver, Fibrosis, Vitamin D

## Abstract

**Background:**

It has been suggested that vitamin D and its receptors involve in suppressing fibrogenic signaling in non-alcoholic fatty liver disease (NAFLD). However, the effect of vitamin D supplementation on fibrogenic factors has not been investigated in NAFLD individuals with steatohepatitis. This study was designed to examine the effects on vitamin D supplementation on serum levels of vitamin D receptor (VDR), fibrogenic factors, and fibrogenic microRNAs (MiR) in NAFLD patients.

**Methods:**

Forty-six NAFLD patients will be recruited in this study. After block matching for sex and BMI, they will be randomly assigned to receive 4000 IU/day vitamin D or placebo for 12 weeks. Weight, height, and waist circumference will be measured. Determination of serum fibrogenic MiRs, laminin, collagen type IV, hyaluronic acid, vitamin D, VDR, calcium, blood glucose, serum insulin, lipid profile, liver markers (ALT, AST, total, direct, and indirect bilirubin) will be done at study baseline and at the end of the trial. Insulin resistance and insulin sensitivity will be determined using the HOMA-IR and QUICKI equation.

**Discussion:**

This is the first randomized controlled trial that will determine the effect of vitamin D supplementation on serum levels of VDR, fibrogenic factors, and fibrogenic MiRs in NAFLD patients. The results of this trial will provide clinical evidence on the effectiveness of vitamin D supplementation in controlling liver fibrosis in NAFLD patients.

**Trial registration:**

Iranian Registry of Clinical Trials, IRCT201405251485N13. Registered on 14 March 2017.

**Electronic supplementary material:**

The online version of this article (10.1186/s13063-019-3241-7) contains supplementary material, which is available to authorized users.

## Background

Non-alcoholic fatty liver disease (NAFLD) is a common progressive metabolic disorder. It starts with simple fatty liver and develops to steatohepatitis, fibrosis, and cirrhosis [1]. This clinical–pathological condition affects approximately 30% of the adult population in both developed and developing countries [2–4].

Findings from an earlier meta-analysis revealed that NAFLD patients had low levels of serum 25 (OH) D_3_. The high prevalence of vitamin D deficiency in these patients contributes to poor outcomes and progression to liver fibrosis [1, 2, 5, 6]. Experimental studies have indicated that vitamin D and its receptor (VDR) involves in suppressing fibrogenic signaling [7]. However, no evidence exists regarding the effects of vitamin D on concentrations of fibrogenic factors and liver fibrosis in NAFLD patients. Previous clinical trials have examined the effects of vitamin D supplementation on serum concentrations of inflammatory markers and lipid profiles in NAFLD patients [8–11]. Moreover, gene expression of some specific microRNAs (MiR) are disregulated in NAFLD. Most of these MiRs are related to lipid and cholesterol metabolism. There is no information about the effects of vitamin D supplementation on fibrogenic MiRs; however, some studies showed that vitamin D and VDR might modulate MiRs. As vitamin D has been shown to influence inflammation and lipid metabolism, it is hypothesized that vitamin D supplements might regulate fibrogenic MiRs in NAFLD patients. This randomized, placebo-controlled, parallel clinical trial was therefore designed to examine the effects of vitamin D supplementation on serum levels of VDR, fibrogenic factors, and fibrogenic MiRs in NAFLD patients with non-alcoholic steatohepatitis (NASH).

## Methods/design

### Participants

This parallel randomized double-blind placebo-controlled clinical trial (RCT) will be done on patients with NASH. Patients will be recruited from the Masoud Internal Specialized Clinic and Imam Khomeini Hospital, affiliated with Tehran University of Medical Sciences, Tehran, Iran. We calculated required sample size based on data from a previous study [12] by considering serum laminin as a key dependent variable, type I error of 0.05, and study power of 90%. Considering the mean difference in serum laminin levels of 136.7 ng/mL between the two groups [12], based on the suggested formula for parallel clinical trials, we reached the sample size of 18 patients in each group. Taking into account a possible drop-out rate of 30%, 23 patients will be enrolled in each group. The study is registered in the Iranian Registry of Clinical Trials website (http://www.irct.ir, identifier: IRCT201405251485N13). This study was reported based on recommended check lists for clinical trials (Additional files 1 and 2).

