### Randomization

Forty-six patients will be enrolled in the whole project. We will use block randomization, in which the assignment will be done based on sex (male/female) and BMI (overweight/obese). Participants will be matched based on sex and BMI into blocks. Therefore, the block size would be four [14, 15]. This method of randomization will provide the equal number of men and women as well as overweight and obese patients that will be assigned to the intervention and placebo groups [14, 15]. Random allocation sequence will be generated using Random Allocation Software: RAS [16]. Given the total sample size of 46 and considering matched cases in terms of sex and BMI, the sample size in each subgroup of gender and BMI will be 12 ± 1. The allocation process of participants into vitamin D and placebo groups will be carried out using computer-generated random sequences by a third person who will not be involved in the project directly.

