### Outcomes

The primary outcomes of the present clinical trial would be serum VDRs, laminin, collagen type IV, hyaluronic acid, MiR-122, MiR-21, and MiR-34a. The secondary outcomes would be liver enzymes, total, direct, and indirect bilirubin, lipid profile, and glycemic indices. We will also examine serum vitamin D and calcium concentrations. All these measurements will be assessed at study baseline and at the end of the trial. Vitamin D supplementation will be considered for the placebo group as post-trial care (Fig. 2).

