### Statistical analysis

Statistical analyses of all data will be performed using SPSS software version 21.0 (SPSS Inc., Chicago, IL, USA). The intention-to-treat approach will be used for data analysis. Data will be expressed as mean ± standard deviations (±SD). The one-sample Kolmogorov–Smirnov test will be used for assessing the normality of the distribution of data. In case of non-normal distribution of a variable, we will apply the log transformation. If the variables were non-normally distributed even, after log transformation, we will use non-parametric tests in the analyses. Repeated measure analysis of variance will be used to identify the effect of the intervention of outcome variables. In these analyses, baseline levels of the outcome variables will be considered as covariates. If any outcome variable was non-normally distributed, we will use the Friedman test. *P* < 0.05 will be considered statistically significant. All analyses will be done by a blind researcher before uncoding the study interventions.

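### Enrolling 23 per group does not cover the stated 30% drop-out: at that rate about 16 per group remain, not 18, and power on the stated calculation falls modestly below 90%

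*Protocol article*

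**What the plan says.** The sample-size statement is in the Participants section of the protocol article. Serum laminin is the key variable, and the inputs are "type I error of 0.05, and study power of 90" per cent and a "mean difference in serum laminin levels of 136.7 ng/mL between the two groups", taken from a cited earlier study. From these, "we reached the sample size of 18 patients in each group". The allowance for loss follows directly: "Taking into account a possible drop-out rate of 30%, 23 patients will be enrolled in each group".

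The total is consistent elsewhere. The Abstract gives forty-six patients, and the Randomization section says "Forty-six patients will be enrolled in the whole project". So 23 per group is not a misprint.

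Two other statements bear on the point. Under Outcomes, "All these measurements will be assessed at study baseline and at the end of the trial". Under Statistical analysis, "The intention-to-treat approach will be used for data analysis", with the baseline level of each outcome as a covariate.

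**The concern.** The usual allowance for drop-out divides the required number by the fraction expected to stay. Multiplying the required number by one plus the drop-out rate gives too small a figure, because the loss applies to everyone enrolled and not only to the number required. The stated 23 looks like the second calculation.

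If so, three of the plan's own figures (18 needed, 30% lost, 23 enrolled) cannot hold together, and the 90% power is not what the design gives at the loss it says it allows for. The stake is interpretive. A reader of a null laminin result would take 90% power as secure up to 30% drop-out, when it is secure only to about 22%. The slip does not bias the treatment estimate, alter the type I error or change the analysis.

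**Working it through.** **Inputs from the document.** Required number per group 18, drop-out 30%, enrolled per group 23, difference 136.7 ng/mL, type I error 0.05, power 90%.

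**Inputs not in the document.** The standard deviation, whether the test is two-sided, and the baseline-to-week-12 correlation. Two-sided testing is assumed below and the one-sided result is shown beside it.

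**Step 1: reproduce the stated figure.** 18 × (1 + 0.30) = 23.4, rounded down to 23. This is the only simple route found to 23.

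**Step 2: the number that 30% loss requires.** 18 / (1 − 0.30) = 25.7, so 26 per group or 52 in total. Check: 26 × 0.70 = 18.2.

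**Step 3: what 23 delivers.** 23 × 0.70 = 16.1, so about 16 per group. The largest loss that leaves 18 is 1 − 18/23 = 5/23 = 21.7%.

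Steps 1 to 3 use only the document's figures. The rest depends on assumptions.

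**Step 4: back-solve the standard deviation.** For n per group, n = 2(1.960 + 1.2816)² / d², where d is the difference divided by the standard deviation. The stated 18 is a whole number, so the unrounded result may lie anywhere from just above 17 to 18.

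- Unrounded 18: d = 3.2416 × √(2/18) = 1.081, SD = 136.7/1.081 = 126.5 ng/mL.
- Unrounded just above 17: d = 3.2416 × √(2/17) = 1.112, SD = 136.7/1.112 = 123.0 ng/mL.

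**Step 5: power at 16 per group.** Power = Φ(d√(16/2) − 1.960).

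| Unrounded n | d | Power at 16 | Difference with 90% power at 16 |
|---|---|---|---|
| 18 | 1.081 | Φ(1.096) = 86.3% | 136.7 × √(18/16) = 145.0 ng/mL |
| just above 17 | 1.112 | Φ(1.185) = 88.2% | 136.7 × √(17/16) = 140.9 ng/mL |

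**Step 6: sensitivity to method.** Using the t test both to back-solve d and to evaluate power gives 86.1 to 88.1% at 16 per group. A one-sided 0.05 test with the normal formula gives 86.7 to 88.4%. Every variant is below 90%, as it must be: if 18 is the smallest number that reaches 90%, 16 does not.

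**Step 7: what baseline adjustment could recover.** Adjusting for a baseline value with correlation r to the final value multiplies the residual variance by (1 − r²). The loss is offset when 1 − r² is no more than 16/18, that is r at least √(1 − 16/18) = 0.33. If 18 was rounded up from just above 17, the threshold is √(1 − 16/17) = 0.24.

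**The case against.** **The loss is small and conditional.** The article calls 30% a possible rate. Up to 21.7% loss, 18 or more per group remain and nothing is lost. At the full 30% the shortfall is two patients per group and about 2 to 4 points of power. This stands, and it limits the severity.

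**The analysis adjusts for baseline.** A correlation of 0.24 to 0.33 would restore the power, and the Statistical analysis section does specify the covariate. This stands as a possibility only. No correlation is given, and the sample-size calculation does not use one.

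**Intention to treat keeps drop-outs in.** This does not rescue the figure. Outcomes are measured only at baseline and at the end of the trial, so a patient who leaves has no final value. The allowance itself also treats drop-outs as lost from the 18.

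**The 30% might mean a share of the 18.** Five extra patients are 5/18 = 27.8% of 18, so even that reading does not quite reach 30%. It is also not what a drop-out rate among enrolled patients means.

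**Stronger readings that the document does not support.** A reader might infer that the trial simply lacks 90% power. That drops the condition, since it follows only if loss exceeds about 22% and adjustment recovers nothing. A reader might also quote power as low as 84%. That figure takes d from the normal formula and evaluates power with the t test; on that mixed basis even 18 per group has only 88.3%, so 84% is not a fall from 90% caused by drop-out. Nor can a single figure such as 86.3% or 145 ng/mL be read off the document, because the standard deviation, the sidedness and the rounding of 18 are not given.

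**Conclusion.** The drop-out allowance is wrong as written. Eighteen after 30% loss needs 26 per group; 23 leaves about 16 and protects 18 only up to about 22% loss. These head-counts rest on the article's own figures, and nothing elsewhere in it (another enrolment figure, a lower drop-out rate or replacement of drop-outs) changes them.

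The effect on power is modest. If 30% drop out, the unadjusted calculation gives about 86 to 88% power for 136.7 ng/mL, or 90% for about 141 to 145 ng/mL. This assumes a two-sided 0.05 test and a standard deviation back-solved from the stated 18 per group. The direction does not depend on the standard deviation; the size does.

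Severity is minor to moderate. The statement should be corrected, but the error does not undermine the trial.

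**What to change.** Restate the sentence in the Participants section and leave enrolment at 46. For example: *With 23 patients enrolled per group, 18 per group will complete if drop-out is no more than about 22%. If drop-out reaches 30%, about 16 per group will remain, and power for a difference of 136.7 ng/mL will be X%.*

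The sponsor should compute X from the standard deviation it used and state that value, the sidedness and the test beside it. The 86 to 88% given here is a guide under the back-solved assumption and should not be copied in as fact. If the sponsor wants to rely on baseline adjustment, the assumed correlation should be stated.

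Enrolling 52 is not proposed. The Trial status section expected recruitment to finish by 15 January 2019, before the article appeared on 4 March 2019. The cost is one sentence and a slightly less favourable statement of drop-out tolerance or power.

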### Inclusion criteria

In this study, we will recruit NAFLD patients with NASH aged 20–60 years, at least six months before enrollment in the study. Diagnosis of fatty liver will be made based on findings from ultrasound reports. Patients will be recruited if they had NAFLD at grade 2 or 3. Having a vitamin D deficiency or insufficiency (serum levels of 25 (OH) vitamin D_3_ < 30 ng/mL) would be another requirement for inclusion in the study [13].

### Exclusion criteria

Individuals who are smokers, those consuming alcohol, are pregnant or lactating, or decided to get pregnant during the next three months will not be included. We also will not include individuals with some pathologic conditions affecting the liver, including viral hepatitis, any acute or chronic liver failure, liver transplantation, cholestasis, hemochromatosis, Wilson disease, α-1 anti-trypsin deficiency, suffering from diabetes, heart failure, renal failure, kidney stones, any neoplasia, inflammatory disease, usual consumption of corticosteroids, non-steroidal anti-inflammatory drugs (NSAIDs), antibiotics, proton pump inhibitors (PPIs) during the last nine months, hormone replacement therapy (HRT) or those taking high doses of estrogen, vitamin D supplements, and antioxidants during the last three months. If a participant gets pregnant during the study, consumes alcohol and/or tobacco, antioxidants, or has weight loss of > 2 kg, he or she will be excluded.

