### Study design

This trial will be done in accordance with the guidelines laid down in the Declaration of Helsinki (1964). The study has already been approved by the bioethics committee of the Tehran University of Medical Sciences (no. IR.TUMS.VCR.REC.1395.1683). At the initial phase, we will screen 300 NAFLD patients, based on the inclusion criteria mentioned above. Those who meet the criteria will be included. All participants will be asked to complete and sign the written informed consent. Before allocating participants into the vitamin D and placebo groups, anthropometric indices, including weight, height, and waist circumference (WC), will be measured and body mass index (BMI) will be calculated. Individual questionnaires including demographic characteristics, past medical, drug and diet history, as well as socioeconomic status (SES) will be completed for each patient through the comprehensive face-to-face interview. To perform biochemical and molecular measurements, 10-mL overnight fasting venous blood samples will be obtained from each patient. All individual information of participants will be secret. A diagram of study design was shown in Fig. 1.

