### Anthropometric assessment

Data on anthropometric indices, including body weight, height, WC, and BMI will be obtained at study baseline and end of the trial. Body weight will be measured in a fasting state, without shoes and wearing light clothing to the nearest 0.1 kg accuracy, using a weighing calibrated scale (Seca, Hamburg, Germany). Height will be measured by mounted tape, without shoes and at a standing position near to the wall to the nearest 0.1 cm accuracy using a stadiometer (Seca, Hamburg, Germany). WC will be measured to the nearest 0.1 cm accuracy by non-stretching tape measure around the abdomen. BMI will be calculated by dividing weight in kilograms by height in meters squared.

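### The in-study exclusion rule (pregnancy, alcohol, tobacco, antioxidants, weight loss over 2 kg) is incompatible with the unqualified intention-to-treat statement, and the two must be reconciled

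*Protocol article*

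**What the plan says.** The Exclusion criteria section does two things. It first lists conditions that bar entry. It then turns to events after entry: "If a participant gets pregnant during the study, consumes alcohol and/or tobacco, antioxidants", or a participant who "has weight loss of > 2 kg, he or she will be excluded". It does not say whether this means exclusion from treatment, from follow-up or from the analysis.

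The Statistical analysis section states: "The intention-to-treat approach will be used for data analysis". It names no other analysis set.

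Three statements on timing bear on the rule:

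- Study design: "Before allocating participants into the vitamin D and placebo groups, anthropometric indices, including weight, height, and waist circumference (WC), will be measured".
- Anthropometric assessment: "body weight, height, WC, and BMI will be obtained at study baseline and end of the trial".
- Outcomes, after listing the primary and secondary outcomes: "All these measurements will be assessed at study baseline and at the end of the trial".

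On numbers, the Participants section requires 18 per group and adds: "Taking into account a possible drop-out rate of 30%, 23 patients will be enrolled in each group".

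**The concern.** Intention-to-treat keeps every randomised participant in the assigned arm, whatever happens afterwards. A rule that removes people for events during the study does the opposite. As the article stands, two analysts could use different analysis sets for the primary outcomes and each cite it in support.

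The weight trigger deserves most attention. Weight change is a post-randomisation variable. The supplement could affect it, and it is plausibly related to the liver, lipid and glycaemic measures. The rule is also one-sided, since a participant who gains more than 2 kg stays in. Selecting on such a variable can undo the balance that randomisation provides, and if part of any effect runs through weight, it removes some of that effect.

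**Working it through.** The article gives no figure for the effect of this rule, so there is none to reproduce. The first two steps compare the text. The last three are illustrations under stated assumptions.

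**1. Is the rule post-randomisation?** Baseline weight is taken before allocation, and the next stated weighing is at the end of the trial. On that schedule, a loss of more than 2 kg can be seen only after randomisation. The other triggers are worded as events during participation.

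**2. Does either reading of excluded fit intention-to-treat?**

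- *Dropped from the analysis:* this contradicts intention-to-treat directly.
- *Withdrawn from the trial:* outcomes are scheduled at baseline and at the end, so a participant withdrawn in between has no post-baseline value unless the week-12 sample is still taken. The article does not provide for that.

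Neither reading yields an as-randomised analysis on observed data.

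**3. How many could the weight trigger remove?** Assume 12-week weight change is normal with mean 0. The share losing more than 2 kg is Φ(−2/SD), applied to 46 participants (23 per group).

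| Assumed SD (kg) | Φ(−2/SD) | Removed of 46 | Left per group of 23 |
|---|---|---|---|
| 1.5 | 9.1% | 4.2 | 20.9 |
| 2 | 15.9% | 7.3 | 19.4 |
| 3 | 25.2% | 11.6 | 17.2 |

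The margin between 23 enrolled and 18 required is 5 per group. At SD 3 kg this trigger alone would take 23 − 17.2 = 5.8 per group.

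**4. When does it bias the comparison?** Let one arm lose δ kg more on average, with SD 2 kg and the same relation of outcome to weight in both arms. Among those kept (change above −2 kg), mean weight change is −δ + 2·φ(a)/(1 − Φ(a)), where a = (−2 + δ)/2.

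- δ = 0: 2 × 0.2420/0.8413 = 0.575 kg; 84% kept.
- δ = 0.5: −0.5 + 2 × 0.3011/0.7734 = 0.279 kg; 77% kept.
- δ = 1: −1 + 2 × 0.3521/0.6915 = 0.018 kg; 69% kept.

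The arm difference in weight falls from −0.5 to 0.279 − 0.575 = −0.296 kg, and from −1 to 0.018 − 0.575 = −0.557 kg. With an assumed slope of 0.2 outcome SD per kg:

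| δ (kg) | All randomised | After exclusion | Share lost |
|---|---|---|---|
| 0 | 0 | 0 | none |
| 0.5 | −0.100 SD | −0.059 SD | 41% |
| 1 | −0.200 SD | −0.111 SD | 44% |

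The share lost does not depend on the slope. With δ = 0 and equal slopes there is no bias between arms. If the slopes differ by arm, bias can arise even with δ = 0.

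**5. Scale against the design effect.** If the 0.05 type I error is two-sided (the article does not say), 18 per group at 90% power implies a standardised effect of (1.960 + 1.282) × √(2/18) = 1.08. The absolute losses in step 4 are 0.100 − 0.059 = 0.041 SD and 0.200 − 0.111 = 0.089 SD.

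**The case against.** The best defence is that the rule stands under eligibility and never says that participants leave the analysis. It may mean withdrawal, which the 30% drop-out allowance could cover. It is true that the term is undefined. But an allowance in the sample size protects power; it does not make an analysis without those participants intention-to-treat.

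Several objections to the size of the problem stand. The weight-change SDs, the arm difference and the slope are not in the article. The trial also tries to keep diet and activity stable, and blinding lessens differential behaviour. Nothing in the article suggests that pregnancy, alcohol, tobacco or antioxidant use responds to blinded tablets, so the bias argument rests on weight alone.

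Three stronger readings are tempting and are not supported:

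- *That the rule selects on trial outcomes.* Weight is not among the listed primary or secondary outcomes.
- *That the analysis must be complete-case because of how SPSS handles missing values in repeated-measures analysis.* The article does not describe missing-data handling, which may sit in a plan not shown. With one post-baseline value, imputation or a mixed model would in any case add little to a baseline-adjusted analysis of those observed.
- *That every participant meeting the weight trigger lacks a week-12 sample.* If the loss is found at the end visit, the sample can exist. Nor does the article say that weight is taken only twice: participants collect tablets at week 6, and the timepoint figure is not shown.

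**Conclusion.** The conflict is real and rests on two printed statements, not on an omission. As written, the article does not settle who is in the primary analysis, and neither reading of the exclusion rule is compatible with intention-to-treat. It should be resolved before the data are analysed.

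The consequence is conditional. About 4, 7 or 12 of 46 participants would be lost to the weight trigger if the SD of weight change is 1.5, 2 or 3 kg with mean 0. Bias between arms needs a difference by arm in weight change or in its relation to outcome. Under the hypothetical set-up above, 41-44% of the weight-mediated component would be lost, or 0.04 to 0.09 SD, which is small beside the effect the trial was sized for. A reader might infer that the result will be biased; the article does not show that.

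**What to change.** Reword the last sentence of the Exclusion criteria section along these lines: participants who meet any of these conditions after randomisation remain in follow-up, give the week-12 sample where possible and are analysed in their assigned group; their exclusion applies only to a labelled per-protocol sensitivity analysis. The Statistical analysis section should name both sets.

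Recruitment was due to finish on 15 January 2019, before the article appeared on 4 March 2019, so rewording may come too late for some participants. For anyone already excluded without a week-12 sample, report numbers and reasons by arm, and do not describe the analysis as full intention-to-treat.

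The cost is a wording change, one extra analysis, continued sampling of a few participants and perhaps slight dilution from those who did not adhere. No new sample size is needed. Whether study tablets continue after one of these events is a clinical matter on which no view is taken here.
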